### Patient characteristics and confounding factors

Key characteristics of patients present in each season of the cohort will be included as confounders in the analyses. Confounders will be defined in each year on the first day of the preinfluenza season (1 September).

*Demographics*: Sex, age band and socioeconomic status will be included in all analyses; socioeconomic status will be measured using quintiles of the Scottish Index of Multiple Deprivation (SIMD). SIMD is an area-based measure of deprivation derived from seven domains including income, employment and education.^31^ Rurality in terms of urban/rural location (one large urban, six remote rural) will also be included in the analysis.

*At-risk groups*: At-risk patients are those with certain comorbidities for whom seasonal influenza vaccination is indicated. Patients will be defined as high risk according to national guidance^29^ if they have one or more of the following conditions:
Asthma;Chronic heart disease;Chronic kidney disease (including renal transplantation) stages 1–2 and 3–5;Chronic liver disease;Chronic neurological diseases;Chronic respiratory diseases;Conditions or drugs causing impaired immune function;Diabetes;Pregnancy (from 2009/2010);Asplenia or dysfunction of the spleen (from 2014/2015);Body mass index (for 2015/2016).

*Chronic diseases*: We will include this for our non-specific clinical outcomes and adverse events. Comorbidity will be defined by the 17 disease categories that constitute the Charlson Comorbidity Index.^32^ This Index has been validated in a number of different databases using codes from healthcare databases.^33^ Furthermore, a study has mapped Read codes from a UK general practice database to the relevant Charlson comorbid disease groups, resulting in a model that performed well in the prediction of 5-year mortality.^34^ These codes will be used to identify comorbidities that are present in a patent's record prior to the start of each preinfluenza season (1 September).

*Smoking status*: This will be derived from primary care data (current smoker, ex-smoker, non-smoker) and determined on 1 September each year.

*Previous vaccinations*: A variable will be included for patients who have received seasonal influenza vaccination in previous seasons to account for the possibility of persisting or reduced VE in the subsequent year.^35^

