### Statistical analysis

Baseline characteristics will be summarised by vaccination status for the whole cohort using mean, median or proportion where appropriate together with a measure of dispersion. We will evaluate the baseline characteristics of those tested and not tested using RT-PCR. Missing data will be reported for each variable. A 5% significance level will be used for hypothesis tests for the primary outcome. All p values will be two sided. All analyses will be undertaken in R (V.3.2.3; R Core Team (2015). R: A language and environment for statistical computing. R Foundation for Statistical Computing, Vienna, Austria. URL https://www.R-project.org).

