### Vaccine effectiveness

#### RT-PCR outcomes

For VE using information from linked virological RT-PCR swab data (a binary event) we will carry out a nested case test-negative control study.^19^ Influenza positivity will be compared with no influenza among patients who have ILI symptoms and tested for influenza. The primary analysis will be through a logistic generalised additive model where the effects of gender, age, socioeconomic status (SIMD^33^) and being in an at-risk morbidity group are adjusted for (a TND study). A spline function for time during each season will be included to model the background rate of influenza and correct for any potential bias associated with the proportions of test-negative and test-positive patients at different periods. VE will be measured by comparing the results from swabs taken after vaccination among those vaccinated to swabs taken among those unvaccinated at the time the swab is collected. Vaccination will be used to define exposure status if it was given at a time point between the 1 September and the end of the influenza season (figure 1). The adjusted estimate of VE=(1**−**OR)×100, where the OR is derived from the coefficient of vaccine status in the model. In our main analysis, we will assess only the first dose when two doses are given. We will carry out analysis stratified by influenza A (H1—including pandemic influenza and H3 subtype where recorded) and B.

We will carry out a number of sensitivity analyses for the primary end point:
*Non-sentinel* versus *sentinel*: We will explore the validity of using laboratory-confirmed influenza tests from non-sentinel primary care and secondary care sources versus sentinel primary care practices. Patient characteristics of individuals swabbed in non-sentinel primary care practices and secondary care will be described and any interaction between source of swab and outcome will be tested.*Negative controls*: As there should be no VE for influenza vaccine for these outcomes, we will explore the use of laboratory-confirmed infections (currently 10 respiratory viruses including rhinovirus and adenovirus) tested using multiplex RT-PCR at the same time as the influenza RT-PCR.*LAIV VE in younger/immunodeficient*: For younger vaccine-naïve or immunodeficient children receiving LAIV, we will account for any second dose in our model.

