### Sample size

We expect a final total sample size of up to 1.25 million from 220 practices. Using data from the PIPER 2014/2015 cohort, which has 263 000 individuals, 16% are aged 2–17, and 18% aged 65+.^48^ Vaccine uptake among children aged 3–12 years is 60% and vaccine uptake among those aged 65+ is 70%. Linked to this cohort from all virology tests in Scotland were 1745 RT-PCR tests overall; 331 RT-PCR tests among 2–17 years old; 366 RT-PCR tests among those aged 65+. This gives a multiplier ratio of around 5:1 from the PIPER cohort to the SIVE II cohort and this is used to estimate the numbers of RT-PCR tests expected each year. We expect 1800 RT-PCR tests per year among those aged 65+, 1650 laboratory tests per year among those aged 2–17. We expect 1745/12×5=630 patients with asthma swabbed per year as about 12% of the population is treated for asthma.

Using data generated from the SIVE project,^49^ we estimate a vaccination rate of 60% among children targeted for receipt of LAIV and a swab positivity rate of 20% among the unvaccinated. This should give 90% power to detect a VE of 31% based on 1650 swabs in one season. Pooling data over two seasons give an estimated 3300 swabs in children eligible for vaccination and a 90% power to detect a VE of 22%.

For 65+ year olds targeted for receipt of TIV where there is a vaccination rate of 70% and a swab positivity rate of 10% among the unvaccinated we anticipate an 80% power to detect a VE of 39% where we estimate that there will be 1800 swabs each year in the later years. During the peak influenza activity when swab positivity might increase to 20% there is a 90% power to detect a VE of 31%. About 1 in 12 of the population is treated for asthma^50^ and we anticipate 1260 swabs among patients with asthma in final two seasons. Assuming 40% are vaccinated and that the swab positivity is around 15% gives 80% power for a VE of 35%. For an influenza type/subtype which has 50% of the total cases, then the detectable VEs will be 40–50% with 90% power. For a type/subtype which has about 25% of the cases, then the detectable VEs will increase to over 60% with 90% power. These powers above do not take into account design effects for the clustering of patients within GP practices. Analyses of the historic PIPER cohorts^48^ has revealed design effect of <7% and this serves to increase the detectable VE by about two percentage points.

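### Age is committed to bands in all analyses although the primary model is already a GAM; a smooth of age would remove possible within-band confounding at almost no cost (minor)

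*Protocol article*

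**What the plan says.** The section on patient characteristics and confounding factors fixes the form of the main demographic covariates for every model: "Sex, age band and socioeconomic status will be included in all analyses". No cut-points are given.

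The RT-PCR outcomes section defines the primary analysis: "The primary analysis will be through a logistic generalised additive model where the effects of gender, age, socioeconomic status" and membership of an at-risk group are adjusted for. Age appears there without a stated form. The one smooth term it names is for calendar time: "A spline function for time during each season will be included to model the background rate of influenza". VE is (1 − OR) × 100, "where the OR is derived from the coefficient of vaccine status in the model".

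The Cox models in the non-specific clinical outcomes section also adjust for age without saying how it is entered. Nowhere does the article mention a continuous or smooth age term.

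**The concern.** In this study age bears on both sides of the comparison. Programme eligibility depends on age, and the Study period section phases the childhood programme in by age. The Sample size section assumes different uptake and different positivity in children ("we estimate a vaccination rate of 60% among children targeted for receipt of LAIV and a swab positivity rate of 20% among the unvaccinated") and in people aged 65+ ("where there is a vaccination rate of 70% and a swab positivity rate of 10% among the unvaccinated"). If both quantities differ between age groups, gradients inside a wide band are plausible. A band indicator removes differences between bands. It leaves whatever association between age, vaccination and positivity remains within a band, and the vaccine coefficient absorbs it.

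Such an error does not shrink with more swabs, and pooling over seasons is foreseen. The plan has already chosen a model class that fits smooth covariates, so the remaining error could be avoided.

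**Working it through.** **Plan's own figures.** The article gives no figure for age confounding. The only stated quantities that enter are uptake, positivity and the detectable VEs. As a check on those inputs, take the children's claim, "This should give 90% power to detect a VE of 31% based on 1650 swabs in one season": 660 unvaccinated and 990 vaccinated swabs, 20% against 0.20 × 0.69 = 13.8%, two-sided 5%, give power 0.911, in line with the stated 90%. That treats VE as 1 − RR; with VE as 1 − OR the power is 0.798. Neither figure depends on how age is entered, so this does not bear on the present point.

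**Assumptions, since the article has no rates by year of age.** Ages are uniform by single year, uptake is linear in age, and log-odds of positivity are linear in age, centred on 10% (65+) or 20% (children). The true OR is 1, so any VE shown is spurious.

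**Formula for one band.** The vaccinated and unvaccinated differ in mean age by Δ = s·σ² / [ū(1 − ū)], where s is the uptake slope per year, σ² = (n² − 1)/12 for n single years of age, and ū is mean uptake. Spurious VE ≈ 1 − exp(βΔ), with β the log-odds slope of positivity per year.

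- *65-90 as one band, uptake 60% to 80%:* σ² = (26² − 1)/12 = 56.25; s = 0.20/25 = 0.008; Δ = 0.45/0.21 = 2.14 years. With OR 0.8 per decade, 1 − exp(2.14 × −0.0223) = 4.7%; with OR 0.7, 1 − exp(2.14 × −0.0357) = 7.4%. The exact logistic fits give 4.6% and 7.2%.
- *65-74 as one band, uptake 65% to 75%:* σ² = 8.25; Δ = 0.0917/0.21 = 0.44 years; 1.0% and 1.5%.
- *2-11 as one band, uptake 55% to 70%:* Δ = 0.1375/0.2344 = 0.59 years. With OR 1.5 and 2.0 per decade, −2.4% and −4.1%.

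**Same scenarios, other ways of entering age (logistic fits on expected counts), spurious VE in points:**

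| Group | One band | Two bands | 5-year bands | Spline, 4 df |
|---|---|---|---|---|
| 65-90, OR 0.8 / 0.7 per decade | 4.6 / 7.2 | 1.3 / 2.0 (cut at 75) | 0.2 / 0.3 | 0.0 / 0.0 |
| 2-11, OR 1.5 / 2.0 per decade | −2.4 / −4.1 | −0.9 / −1.6 (2-4/5-11) | not shown | 0.0 / 0.0 |

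**Effective vaccine, 65+.** True VE 39%, uptake rising from 50-60% to 80-85%, positivity sloping between 6% and 14% in either direction. One band gives 35.4% to 44.8%, two bands 37.8% to 40.9%, 5-year bands 38.9% to 39.2%.

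**Bands and eligibility ages, children 2-17.** True VE 31%, uptake 55-65% to age 11 and 5-10% from age 12, positivity sloping between 10% and 30%:

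- 2-4/5-11/12-17, cut where uptake drops: 30.9% to 31.0%.
- 2-4/5-14/15-17, straddling the drop: 25.6% to 41.6%.
- 2-4/5-17: 20.9% to 48.1%, up to 17 points from the truth.
- Spline of age with 4 df and no eligibility indicator: 31.0% to 31.1%.
- Flat positivity: 31.0% under every banding.

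The spline does well here partly because positivity was assumed smooth in age. A sharp step in positivity at some age would not be followed exactly.

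**The case against.** The strongest case against is that the harm depends on details the article does not state. Cut-points are commonly left to the analysis plan, and their absence is no error. The RT-PCR outcomes section says age and not age band, so a smooth or fine-grained term is not excluded. The age gradients are assumed, their direction differs between the examples, and with ordinary bands the error nearly vanishes. It is also small against sampling error. With 1800 swabs, 70% uptake and 10% positivity, the standard error of the log OR at no effect is 0.171, so the 95% interval for VE runs from about −40% to +29%. With 1650 child swabs, 60% uptake and 20% positivity, it runs from about −28% to +22%.

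All of this stands as a limit on size. A reader might infer that, because VE is reported for children and for 65+, those groups are the adjustment bands and an error of 5 to 7 points is to be expected. The documents do not support that: a reporting subgroup is not an adjustment band, and narrower bands can be fitted inside it. A reader might equally take the figure of 17 points as a prediction. It needs a wide band across an eligibility age, which the article nowhere proposes.

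The objection does not remove the commitment to bands in all analyses, nor the fact that a smooth term does at least as well in every scenario above without depending on where cuts fall.

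**Conclusion.** The point holds as a minor, free improvement. The article commits age to bands in all analyses and names a smooth only for time; that this governs the primary GAM is inferred from the covariate section. Under the assumed gradients, residual confounding is about 0 to 0.3 VE points with 5-year bands in 65+ and about 1 to 2 points with two bands in 65+ or 2-4/5-11 in children. It is about 5 to 7 points (65+) or −2 to −4 points (ages 2-11) if each is one band, more if a band straddles an eligibility age, and zero if positivity does not vary with age within a band. It would be too strong to say that the planned VE is biased: neither the cut-points nor the gradients are in the documents.

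**What to change.** In the primary GAM, enter age in years as a penalised smooth beside the smooth for time. In the Cox models, enter age as a spline. Keep age bands for tables and subgroup reporting, and amend the covariate section so that it and the model sections state the same form.

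No separate eligibility indicator is needed. A jump in uptake does no harm when the outcome model is right in age, as the age-12 scenario shows. Given age, eligibility acts mainly on vaccination, so adjusting for it could cost precision.

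The cost is one model term and a few degrees of freedom. No new data are required: the Study period section already selects children by single year of age, so age in years must be held.

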**Methods and analysis:**

Test negative and cohort study designs will be used to estimate VE. A primary care database covering 1.25 million people in Scotland for the period 2000/2001 to 2015/2016 will be linked to the Scottish Immunisation Recall Service (SIRS), Health Protection Scotland virology database, admissions to Scottish hospitals and the Scottish death register. Vaccination status (including LAIV uptake) will be determined from the primary care and SIRS database. The primary outcome will be influenza-positive real-time PCR tests carried out in sentinel general practices and other healthcare settings. Secondary outcomes include influenza-like illness and asthma-related general practice consultations, hospitalisations and death. An instrumental variable analysis will be carried out to account for confounding. Self-controlled study designs will be used to estimate the risk of adverse events associated with influenza vaccination.

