**Figure 1 BMJOPEN2016014200F1:**
[figure not shown]
Relationship of first influenza season (2000–2001) to preinfluenza, postinfluenza and non-influenza season periods. Baseline characteristics for each patient are determined on 1 September each year. The earliest date of influenza vaccination varied for each influenza season, but always occurred after 1 September.

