### Exposure definition

For people in at-risk groups, influenza vaccinations (Trivalent Influenza Vaccine (TIV) and LAIV for preschool children aged ≥2 years) are free and administered by general practice.^29^ Data on influenza vaccination carried out in general practice (including CHI and date of administration) are recorded to enable reimbursement. Information on individuals receiving LAIV in schools is collated in the SIRS database and will be extracted for this analysis.^21^ Vaccination will be used to define exposure status if it is given at a time point between 1 September and the end of the influenza season (figure 1). An individual will be defined as vaccinated 14 days after the seasonal influenza vaccine has been administered.^30^ The time period from the first day of the influenza season to day 14 postvaccination will be defined as ‘unexposed’ and the period from day 14 postvaccination until the end of the influenza season will be defined as ‘exposed’. Therefore, those vaccinated between the start of the preinfluenza period up until 14 days before the influenza season will be defined as ‘exposed’ for the duration of the influenza season. We will exclude participants vaccinated <14 days prior to the RT-PCR test as a sensitivity analysis.

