^36^ Adjustment for previous pneumococcal vaccination at any time in the primary care record prior to 1 September each year will also be undertaken.

*Previous healthcare usage*: Measures of previous healthcare resource use will also capture other aspects of chronic health status and include previous years general practitioner (GP) consultations, prescriptions (repeat) and number of admissions to hospital.

*Functional status*: There is no direct measure of functional status made in any of these national databases. However, individuals who are resident in some form of institutional care setting can be identified from the primary care database. This will also be used as an indicator of more severe functional limitation.

*Practice*: Accounting for the clustering of patients within GP practices, we will investigate whether practice characteristics (eg, training practice, list size, type of contract, etc) are associated with vaccine uptake.

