#### Non-specific clinical outcomes study

To determine the effect of vaccination status on influenza-related primary care consultations, hospital admissions and deaths, secondary analyses will be undertaken using non-specific clinical outcomes derived from primary and secondary care. Influenza-like illness (ILI) and otitis media consultation will be derived from the general practice database. Hospitalisation and cause of death from influenza or pneumonia will be derived from SMR01. We will also include in our secondary analysis a range of asthma-related outcomes, for example, asthma-related consultations/symptoms or measurements, hospitalisations/deaths, rescue medications, etc.

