#### Non-specific clinical outcomes

We will estimate VE for non-specific clinical outcomes: primary care consultations for ILI; all-cause emergency hospitalisation and death; and emergency hospitalisation and death due to influenza/pneumonia. Hospital admissions and consultations can have multiple events and each event will be counted.

For this proposal we have adopted methods we found in previous studies to be optimal for measuring VE and accounting for bias and confounding.^47^ Adjusted rate ratios of VE for prevention of hospitalisation/death/general practice consultation will be derived from time-dependent Cox models, taking into account the time at risk and the possibility of multiple events (not for death). Models will include a cluster term to account for intrapractice correlation. These models will adjust for gender, age, deprivation and clinical risk group and exposure to vaccination in each season included as a time-dependent covariate. Each season, individuals will begin in the unvaccinated group (and will accumulate time at risk) until 14 days after the receipt of the vaccine; then they will switch to the vaccinated group.

In all models used to estimate the VE, we will adjust for variables associated with the receipt of a vaccination and effect modifiers, such as vaccinations, consultations and hospitalisation in the previous influenza season, SIMD, urban/rural status, smoking status, Charlson score and pregnancy.

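### Pneumococcal vaccination is coded as of 1 September, so a first dose given in the same autumn as influenza vaccine counts as absent in the pneumonia-outcome models

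*Protocol article*

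**What the plan says.** Under Patient characteristics and confounding factors, the protocol article sets one date for all covariates: "Confounders will be defined in each year on the first day of the preinfluenza season (1 September"). Pneumococcal vaccination appears there under previous vaccinations: "Adjustment for previous pneumococcal vaccination at any time in the primary care record prior to 1 September each year will also be undertaken".

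Influenza vaccination is timed differently. Under Exposure definition, the window closes when the season does: "Vaccination will be used to define exposure status if it is given at a time point between 1 September and the end of the influenza" (…). The legend to Figure 1 adds: "The earliest date of influenza vaccination varied for each influenza season, but always occurred after 1 September". The Cox models described under Non-specific clinical outcomes have "exposure to vaccination in each season included as a time-dependent covariate". A person moves to the vaccinated group 14 days after the dose.

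The outcomes of those models include "emergency hospitalisation and death due to influenza/pneumonia", together with all-cause admission and death and consultations for influenza-like illness. They are secondary: the Non-specific clinical outcomes study section says that "secondary analyses will be undertaken using non-specific clinical outcomes derived from primary and secondary care". The abstract defines the primary outcome: "The primary outcome will be influenza-positive real-time PCR tests carried out in sentinel general practices and other healthcare settings".

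**The concern.** The plan accepts that pneumococcal vaccination needs adjustment, and it estimates VE on an outcome that includes pneumonia. It then measures pneumococcal status at a date that comes before every influenza vaccination of the season. A first pneumococcal dose given with influenza vaccine, or within weeks of it, is invisible to the model until the next 1 September. Influenza vaccination in the same window is followed day by day.

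Suppose these doses go more often to people who attend for influenza vaccine, and suppose they protect against pneumonia. Part of that protection would then be counted as influenza VE. The error would favour the vaccine, and it would fall on the outcomes that the plan already regards as less specific.

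**Working it through.** **Step 1: how one person is coded.** Take someone with no pneumococcal record on 1 September who receives both vaccines that autumn.

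| | Pneumococcal covariate | Influenza exposure |
|---|---|---|
| 1 September | absent | unexposed |
| From 14 days after the influenza dose to the end of that season | absent, although a dose is on record | exposed |
| Next 1 September | present | assessed afresh |

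This follows from the passages set out above and needs no outside fact. Because the covariate counts a dose at any earlier time, each person is miscoded for one season at most. People vaccinated in earlier years are coded correctly.

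**Step 2: direction and size.** The article gives no figure to reproduce, so every input here is an assumption:
- p1 and p0: the shares of influenza-vaccinated and influenza-unvaccinated people with a first, same-autumn pneumococcal dose. Assumed 2–10% and 0–2%.
- e: the proportion by which that dose lowers the influenza/pneumonia outcome. Assumed 10–40%.

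The omitted dose multiplies the influenza rate ratio by

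B = (1 − e·p1) / (1 − e·p0),

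and apparent VE = 1 − (1 − true VE) × B. With true VE of zero, the spurious VE is 1 − B:

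| p1 / p0 | e = 10% | e = 20% | e = 30% | e = 40% |
|---|---|---|---|---|
| 2% / 0% | 0.2 | 0.4 | 0.6 | 0.8 |
| 5% / 1% | 0.4 | 0.8 | 1.2 | 1.6 |
| 10% / 2% | 0.8 | 1.6 | 2.4 | 3.2 |
| 10% / 0% | 1.0 | 2.0 | 3.0 | 4.0 |
| 5% / 5% | 0 | 0 | 0 | 0 |

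(Percentage points.) Two entries worked through:
- 10% / 2%, e = 30%: B = (1 − 0.03)/(1 − 0.006) = 0.970/0.994 = 0.976, so 2.4 points.
- 10% / 0%, e = 40%: B = 1 − 0.04 = 0.96, so 4.0 points.

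Where the vaccine does work, the shift shrinks by the factor (1 − true VE). At a true VE of 30%, the two ends of the range give 1 − 0.7 × 0.998 = 30.1% and 1 − 0.7 × 0.96 = 32.8%.

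**Step 3: do the other safeguards cover it?**
- The analysis for an unmeasured confounder varies its prevalence in each group and its effect on the outcome. These are the p1, p0 and e above, so it has the right form. It is not tied to pneumococcal vaccine, though, and it models hypothetical values for something the primary care record dates.
- The instrument under exploration is area-level influenza vaccine uptake. If areas with high influenza uptake also have high pneumococcal uptake, it would carry the same bias. The documents do not say whether they do.
- The negative-control infections belong to the RT-PCR study and do not test the pneumonia outcomes.

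**The case against.** The strongest reply is that the coding is coherent for what the plan calls it. Pneumococcal vaccination is listed as a previous vaccination among baseline confounders and treated like every other covariate. Measuring covariates before exposure is a sound convention, because it avoids adjusting for consequences of the exposure. This stands as a general rule and shows that the plan does not contradict itself. It is weaker here, because a pneumococcal dose given at about the same time is a concurrent exposure and not a consequence of influenza vaccine.

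The second reply is that the bias needs three facts the documents do not give: that first doses are common in autumn, that they are commoner among influenza vaccinees, and that they reduce the outcome. This stands in full. A reader might infer from the coding that a pneumococcal effect certainly is credited to influenza vaccine. The documents establish the coding gap, not that effect.

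The third reply concerns the remedies. If both vaccines are given on the same day, those people add little to separating the two effects, and the pneumococcal coefficient rests mainly on earlier doses. Its use then assumes that older and newer doses act alike, and it may carry confounding of its own. This limitation stands. Excluding every person-season with a same-season dose would also be unsound: it conditions on an event after follow-up begins, since someone who dies early cannot receive the dose and so stays in. Censoring at the dose avoids that.

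The article also discloses residual confounding in general terms. That is fair, but it does not replace the use of dates already on record.

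**Conclusion.** The concern holds in a limited form. It is certain from the text that a first pneumococcal dose given after 1 September is coded absent for that season, in models whose outcomes include pneumonia admission and death. It is conditional that this inflates influenza VE. Under the assumed inputs the inflation is about 0.2–4 percentage points, and it is zero if uptake is equal in both groups or if the dose has no effect.

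Three stronger readings are tempting, and the documents support none of them:
- **That the main result is affected.** The primary outcome is RT-PCR-confirmed influenza in a test-negative design, and no bias is shown there.
- **That the bias reaches 4–19 points.** Those values come from assuming that 30–50% of newly eligible influenza vaccinees against 2–3% of non-vaccinees have the dose, with an effect of 15–40%: 1 − 0.955/0.997 = 4.2 points and 1 − 0.80/0.988 = 19.0 points. The article plans no analysis of newly eligible people; its named groups are those aged 65 and over, people with asthma or other comorbidities, and pregnant women.
- **That some seasons are worse because pneumococcal vaccine was first offered widely then.** The article says nothing about when or to whom it was offered.

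This is a worthwhile refinement of secondary analyses and does not threaten the study's main conclusion.

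**What to change.** For the Cox models of the non-specific clinical outcomes:

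1. Enter pneumococcal vaccination as a time-dependent covariate that switches at its recorded date. Doses before 1 September are coded present from the start. If the baseline coding is kept for the main model, prespecify this version as a sensitivity analysis.
2. Add a check on the influenza/pneumonia outcomes that censors follow-up at a same-season pneumococcal dose and does not drop the whole person-season.
3. Report the proportion with a first same-season pneumococcal dose by influenza vaccination status. This replaces the assumed p1 and p0 with observed values and shows at once whether the issue matters.

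The cost is analysis wording and programming. A before-1-September rule already requires dated records, so no new data source is needed. The price is statistical: where both vaccines are given on the same day, the pneumococcal coefficient is identified mainly from earlier doses, and censoring loses some vaccinated person-time. Reporting the two analyses side by side makes those limits visible.
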